## Abstract

**Background:**

Hyperuricemia is a risk factor for the onset of chronic kidney disease (CKD) and is significantly associated with the progression of CKD. However, there is no sufficient evidence by interventional research supporting a cause-effect relationship. Hyperuricemic patients without gouty arthritis, whose serum urate (SUA) concentration is ≥8.0 mg/dL and who have a complication, are treated by pharmacotherapy in addition to lifestyle guidance. Nevertheless, there is no evidence that rationalizes pharmacotherapy for patients with hyperuricemia who have no complication and whose SUA concentration is below 9.0 mg/dL.

**Methods/Design:**

The FEATHER (*FE*buxostat *versus* placebo r*A*ndomized controlled *T*rial regarding reduced renal function in patients with *H*yperuricemia complicated by ch*R*onic kidney disease stage 3) study is a prospective, multicenter, double-blind, randomized, placebo-controlled trial of febuxostat—a novel, nonpurine, selective, xanthine oxidase inhibitor. The present study will enroll, at 64 medical institutions in Japan, 400 Japanese patients aged 20 years or older who have hyperuricemia without gouty arthritis, who present CKD stage 3, and whose SUA concentration is 7.1-10.0 mg/dL. Patients are randomly assigned to either the febuxostat or the control group, in which febuxostat tablets and placebo are administered orally, respectively. The dosage of the study drugs should be one 10-mg tablet/day at weeks 1 to 4 after study initiation, increased to one 20-mg tablet/day at weeks 5 to 8, and elevated to one 40-mg tablet/day at week 9 and then maintained until week 108. The primary endpoint is estimated glomerular filtration rate (eGFR) slope. The secondary endpoints include the amount and percent rate of change in eGFR from baseline to week 108, the amount and percent rate of change in SUA concentration from baseline to week 108, the proportion of patients who achieved an SUA concentration ≤6.0 mg/dL, and the incidence of renal function deterioration.

**Discussion:**

The present study aims to examine whether febuxostat prevents a further reduction in renal function as assessed with eGFR in subjects and will (1) provide evidence to indicate the inverse association between a reduction in SUA concentration and an improvement in renal function and (2) rationalize pharmacotherapy for subjects and clarify its clinical relevance.

**Trial registration:**

UMIN Identifier: UMIN000008343

## Background

Hyperuricemia is defined as 'serum urate (SUA) concentration >7.0 mg/dL’ [1]. The prevalence of hyperuricemia is 21.5% in Japanese adult men, and hyperuricemia prevails most in patients in their 30s and 40s; the prevalence of hyperuricemia is 30% in patients in their 30s [2]. Hyperuricemia is a risk factor for the onset of chronic kidney disease (CKD) [3] and is significantly associated with the progression of CKD [4,5]. Persisting hyperuricemia causes the tissue deposition of monosodium urate monohydrate crystals in extracellular fluids of the joints and other sites and induces urate deposition diseases (e.g., gouty arthritis, tophi, kidney injury, and urolithiasis) [6,7]. Women are at higher risk of experiencing the progression of reduced renal function at an SUA concentration ≥6.0 mg/dL that is lower than the conventional definition of hyperuricemia [3], and hyperuricemia influences the progression of kidney injury at the early phase of CKD [8]. In addition to the provision of lifestyle guidance (diet therapy, drinking restriction, encouragement of physical activity, patient education on treatment objective, and management of comorbidities), pharmacotherapy with urate-lowering drugs is recommended for (1) hyperuricemic patients with gouty arthritis or tophi, for (2) hyperuricemic patients whose SUA concentration is 8.0 mg/dL or higher and who have a complication (e.g., kidney injury, urolithiasis, hypertension, ischemic heart disease, diabetes mellitus, metabolic syndrome), and for (3) hyperuricemic patients whose SUA concentration is 9.0 mg/dL or higher and who have no complications [9].

Allopurinol, a purine inhibitor of xanthine oxidase (XO) conventionally used for urate-lowering therapy (ULT) to inhibit uric acid synthesis, was suggested to slow a reduction in renal function compared with the control group in a 12-month, prospective, randomized controlled trial (RCT) in 54 hyperuricemic patients with CKD [10] and delayed a reduction in renal function compared with the control group in a 24-month, prospective RCT in 113 patients with CKD stage 3 [11]. Because of the open-label nature, however, these small-size single-center clinical studies did not provide sufficient evidence about the effect of allopurinol to prevent renal function reduction.

A novel urate-lowering drug, febuxostat, is a potent non-purine selective inhibitor of XO and inhibits both the reduced and oxidized forms of the enzyme in contrast to allopurinol that inhibits the reduced form of the enzyme only [12]. Febuxostat is metabolized mainly by glucuronidation and oxidation in the liver [13], has its dual (urinary and fecal) pathways in excretion (urinary and fecal excretion rates: 49.1% and 44.9%, respectively) [14], and is effective and well tolerated in patients with mild to moderate renal and hepatic impairment [15]. A 28-day, Phase II, randomized clinical trial of febuxostat in 153 patients with gout [16] indicated that treatment with febuxostat significantly reduced SUA concentrations at doses of 40, 80, and 120 mg daily and was safe and well tolerated. The post-hoc analysis [17] of a clinical study on the long-term (5-year) oral administration of febuxostat in 116 patients with hyperuricemic gout [18] revealed that the maintenance of or an improvement in eGFR was inversely correlated with a quantitative reduction in SUA from baseline. Therefore, we presumed that continuous lowering of SUA concentrations might deter a further reduction in renal function of patients with hyperuricemia and/or gout and recognized the importance of prospectively evaluating the long-term effect of SUA reduction on renal function in hyperuricemic patients with impaired renal function.

The objective of the present study is to examine whether febuxostat prevents a further reduction in renal function as assessed with eGFR in Japanese patients with hyperuricemia, who have never had gout and are complicated by CKD stage 3.

## Methods/Design

### Study design and study organization

The FEATHER study is a prospective, multicenter, double-blind, randomized, placebo-controlled clinical study (Figure 1). The recruitment of patients started in November 2012 and concluded in December 2013. The scheduled study period including the 1-year recruitment period is 3 years. Steering Committee (Additional file 1) prepared the protocol and will assume the roles, including the solution of interpretational questions about the protocol, the adjustment of study details among medical institutions, and other tasks. Executive Committee will assume the roles, including the conduct and administration of the entire study, the regulatory check of study progress, the examination of study-propelling measures, the recognition of problems in conducting the study, the discussion on problem-solving measures, the adjustment of publication (article contribution and academic announcement), and other tasks. Independent Data and Safety Monitoring Committee will assume the roles, including the monitoring of study progress, the assessment of safety data at appropriate intervals, the recommendation to continue, adjust, or discontinue the study, and other tasks. The study was approved by Ethics Review Boards of the participating medical institutions (Additional file 2) and is being conducted according to the Declaration of Helsinki. All patients should provide written informed consent before enrollment.

**Figure 1 F1:**
[figure not shown]
Flow diagram of the FEATHER study.

### Patients

The FEATHER study will consecutively recruit, at 64 medical institutions in Japan, 400 Japanese patients with hyperuricemia who have never had gout and are complicated by CKD stage 3a or 3b, who are aged 20 years or older, and who have no gouty arthritis (Table 1).

**Table 1 T1:** Inclusion and exclusion criteria

**Inclusion criteria**	**Exclusion criteria**
1. Men and women	1. Uncontrolled diabetes mellitus; HbA_1c_: ≥8.0% (JDS) or ≥8.4% (NGSP)
2. Age ≥20 years at informed consent	2. Systolic blood pressure ≥160 mmHg or diastolic blood pressure ≥100 mmHg
3. Patients with hyperuricemia; serum uric acid: 7.1-10.0 mg/dL	3. ALT or AST: greater than twice the upper limit of institutional reference range
4. eGFR: 30–59 mL/min/1.73 m^2^ (CKD stages 3a and 3b)	4. Change in serum creatinine level by more than 50% within 12 weeks before the confirmation of eligibility
5. No history of gout	5. Acute renal disease, nephrotic syndrome, other serious disease, dialysis, or renal transplantation
6. Written informed consent for study enrollment obtained from the patient	6. Complication or history of malignant tumor (not excluded from the study when the malignant tumor is not treated within 5 years and if there is no recurrence)
	7. History of hypersensitivity to febuxostat
	8. Intake of any one or more of the following drugs at the confirmation of eligibility: mercaptopurine hydrate, azathioprine, vidarabine, and didanosine
	9. Intake of any one or more of the following urate-lowering drugs within 4 weeks before the confirmation of eligibility: allopurinol, benzbromarone, probenecid, bucolome, and febuxostat
	10. Initiation of intake, dose modification, or discontinuation of intake of any one or more of the following drugs within 4 weeks before the confirmation of eligibility: losartan, fenofibrate, thiazide diuretics, and loop diuretics
	11. Continuous intake of salicylic acid drugs, e.g., aspirin (the patient taking low-dose aspirin [≤324 mg/day] need not to be excluded from the study)
	12. Hormone replacement therapy with estrogens
	13. Pregnancy, nursing, or planed pregnancy during the study
	14. Enrollment in other clinical trials within 24 weeks before providing informed consent
	15. Ineligibility at the investigator’s discretion

CKD, chronic kidney disease; Hba1c, hemoglobin A1c; JDS, Japan Diabetes Society; NGSP, National Glycohemoglobin Standardization Program.

### Treatment

#### Study treatment

Patients are randomly assigned to either of the febuxostat or the control group, in which febuxostat tablets and placebo are administered orally, respectively. Patients in the study groups will receive the allocated study drug for 108 weeks. The dose of the study drugs should be one 10-mg tablet/day at weeks 1 to 4 after study initiation, increased to one 20-mg tablet/day at weeks 5 to 8, and elevated to one 40-mg tablet/day at week 9 and then maintained until week 108.

#### Concomitant therapy

During the study period, the investigator provides the enrolled patient with lifestyle guidance (recommendation for diet management, restriction of alcohol consumption, and encouragement of exercise) by use of a leaflet prepared for this study. The administration of urate-lowering drugs (allopurinol, benzbromarone, probenecid, bucolome, and febuxostat except for study treatment) and contraindicated drugs of febuxostat (mercaptopurine hydrate, azathioprine, vidarabine, and didanosine) is prohibited during the study period.

#### Blinding

All parties involved in the present study (patients, investigators, and data analysts) will be blinded to the allocation of the study drugs—febuxostat tablets and placebo. Serum and urinary urate concentrations will be measured at the central laboratory. The measured values of serum and urinary urate will be concealed to the investigator and patient in an attempt to keep the allocation blinded. Laboratory tests at respective medical institutions will exclude the measurement of SUA concentration and urinary urate concentration from the assessment items. Furthermore, the following actions will be taken to ensure the safety of the patient when SUA concentrations change as described below:

1. The investigator will be informed when SUA concentrations measured at the central laboratory exceeded 12.0 mg/dL in a patient and will discontinue this study for the relevant patient;

2. Independent Data and Safety Monitoring Committee will monitor SUA concentrations and will examine a trend, if detected, to increase in SUA concentrations in each study group; and

3. The investigator will be informed when SUA concentrations decreased to 2.0 mg/dL or lower in a patient and will address the change appropriately.

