#### Endpoints

The primary endpoint of the FEATHER study is eGFR slope (change in eGFR per year, mL/min/1.73 m^2^/year) during the 108-week study period. The eGFR is calculated with the following equation defined by the Japanese Society of Nephrology: eGFRcreat (mL/min/1.73 m^2^) = 194 × [serum creatinine (mg/dLs) measured by the enzyme method]^-1.094^ × age^-0.287^ (× 0.739 if the patient is female).

The secondary endpoints are as follows: (1) the amount (mL/min/1.73 m^2^) and rate (%) of change in eGFR from baseline to weeks 24, 48, 72, and 108; (2) the amount (mg/dL) and the rate (%) of change in SUA concentration from baseline to week 108; (3) the proportion of patients whose SUA concentration became ≤6.0 mg/dL; (4) the incidence of renal deterioration defined by the commencement of dialysis or doubled serum creatinine concentration; (5) changes in biomarkers for renal function (serum cystatin C), oxidative stress (urinary 8-hydroxydeoxyguanosine and urinary L-type fatty acid-binding protein), and inflammation (serum C-reactive protein), as well as in variables for cardiovascular events (12-lead electrocardiogram, serum N-terminal pro-brain natriuretic protein, and albumin urine/creatinine ratio) to monitor the outcomes of ULT from baseline to week 108; (6) incidence of gouty arthritis; and (7) incidence of adverse events (AEs).

For safety assessment, AEs should be evaluated on clinical examination and in laboratory tests. The enrolled patient should visit the institution once every 4 weeks during the first 3 months and once every 3 months thereafter (Table 2). The investigator should evaluate patient compliance through history taking at each visit.

**Table 2 T2:** Schedule for observation, testing, and assessment

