		**Timing**													
**Items**		**Eligibility confirmation**	**Enrollment and assignment**	**Baseline**	**Treatment phase**										
Visit^a^		1		2	3	4	5	6	7	8	9	10	11	12	13
Week after treatment onset^a^		-4		0	4	8	12	24	36	48	60	72	84	96	108
Acquisition of informed consent		X													
Pregnancy test^b^, gender, and date of birth		X													
Smoking history, anamnesis, and complications				X											
Status of study drug intake					X	X	X	X	X	X	X	X	X	X	X
Status of concurrent therapy^c^		X		X	X	X	X	X	X	X	X	X	X	X	X
Commencement of dialysis					X	X	X	X	X	X	X	X	X	X	X
Development of gouty arthritis					X	X	X	X	X	X	X	X	X	X	X
Development of adverse events					X	X	X	X	X	X	X	X	X	X	X
Height (second visit only), body weight, and BMI				X						X					X
Blood pressure (systolic, diastolic) and pulse rate		X^d^		X	X	X	X	X	X	X	X	X	X	X	X
12-lead electrocardiogram				X^e^											X^f^
Hematology blood chemistry^g^, and urinalysis^h^		X^d^		X	X	X	X	X	X	X	X	X	X	X	X
Blood	Serum urate^i^ and creatinine concentrations	X^d^		√	√	√	√	√	√	√	√	√	√	√	√
	T-C, HDL-C, and TG			√ at fasting											
	HbA1c	X^j^		√						√					√
	Markers^k^			√						√					√
Urine	Urinary creatinine, albumin, and urate^i^ concentrations			√						√					√
	Markers^k^			√						√					√
Blood sampling volume for measurement at the central laboratory (mL)				16	10	10	10	10	10	16	10	10	10	10	16

X: Measurement at the institution’s laboratory; √: Measurement at the central laboratory.

^a^Corresponds to the time of completion, discontinuation, or withdrawal.

^b^For the premenopausal female patient only.

^c^Antihypertensives, antihyperlipidemics, antidiabetics, non-steroidal anti-inflammatory drugs, adrenocortical steroids, theophylline, colchicine, and part of contraindicated and restricted concurrent therapies.

^d^Blood pressure, serum urate concentration, serum creatinine concentration, alanine aminotransferase, and aspartate aminotransferase are required to confirm eligibility. Urine protein (qualitative) is required to adjust allocation.

^e^Data obtained within 6 months before consent acquisition should be acceptable, unless cardiovascular or other events have developed. Data within 3 months before and after study completion should be acceptable.

^f^Red blood cell count, white blood cell count, platelet count, hemoglobin, and hematocrit.

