### Statistical methods and sample size

The statistical analysis of the primary endpoint should be made to demonstrate the superiority of febuxostat to placebo. The linear regression line will be fitted to the longitudinal data of the eGFR for each patient. In patients with CKD stage 3, the intergroup difference in the eGFR slope should be compared between the febuxostat group and the control group according to Student’s t-test (analysis of variance), with the stratified adjustment of stages 3a and 3b. Subgroup analysis by stage 3a and 3b should be conducted to check the heterogeneity of the effect size.

Based on previous study results [11,19], we calculated a sample size of 89 patients to detect a difference of 2.7 mL/min/1.73 m^2^/year in eGFR slope between the study groups at each CKD stage (3a or 3b), with a standard deviation of 7.2, a power of 80%, and a one-sided significance level of 0.05. This sample size will provide 94.2% power at a two-sided significance level of 0.05 to perform intergroup comparisons in the overall cohort of patients with CKD stage 3 (178 patients per study group; 356 patients in total). Assuming a withdrawal rate of 11%, the target number of patients is 100 in the subgroups of patients with CKD 3a and 3b, respectively, leading to 200 patients required for the study groups, respectively, and to a total of 400 patients with CKD stage 3.

Efficacy analysis should be performed on an intention-to-treat principle basis. All patients, who took at least one dose of the study drug and who have at least one measurement of the eGFR after study drug administration, should be included in the efficacy analysis set. All patients who took at least one dose of the study drug should be included in the safety analysis set. The interim analysis is not planned in this study. The data to be collected in the present study will be managed and analyzed by the following organization that is completely independent from the present study’s organizations: Non-Profit Organization Japan Clinical Research Support Unit.

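### The SUA >12.0 mg/dL rule ends study participation, almost only on placebo, which conflicts with the intention-to-treat basis; the expected effect is small and the repair is cheap

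*Protocol article*

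**What the plan says.** All references are to the protocol article.

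- **Blinding.** SUA is measured centrally and concealed. The investigator is told when it "exceeded 12.0 mg/dL in a patient and will discontinue this study for the relevant patient". The rule at the low end differs: the investigator is told when "SUA concentrations decreased to 2.0 mg/dL or lower in a patient and will address the change appropriately", and no removal is stated.
- **Table 1.** Entry requires "Patients with hyperuricemia; serum uric acid: 7.1-10.0 mg/dL".
- **Endpoints.** The primary endpoint is "eGFR slope (change in eGFR per year, mL/min/1.73 m^2^/year) during the 108-week study period".
- **Statistical methods and sample size.** "Efficacy analysis should be performed on an intention-to-treat principle basis". "The linear regression line will be fitted to the longitudinal data of the eGFR for each patient". Slopes are compared by Student's t-test (analysis of variance) adjusted for stage 3a/3b, and no weighting is stated. Patients with at least one dose "who have at least one measurement of the eGFR after study drug administration, should be included in the efficacy analysis set".
- **Table 2.** Footnote a, attached to the visit and week row labels, reads "Corresponds to the time of completion, discontinuation, or withdrawal". Serum urate and creatinine are both measured centrally at baseline and at every later visit.
- **Concomitant therapy.** Other urate-lowering drugs are prohibited during the study period.

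Nothing in the article provides for eGFR collection after a patient is discontinued under the SUA rule.

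**The concern.** Intention-to-treat implies that randomised patients are followed for the outcome whatever happens to their treatment. The SUA rule takes a patient out of the study on a value measured after randomisation, and that value is the one the active drug is meant to lower. The removal is therefore tied to treatment arm by construction. The Background section also treats hyperuricemia as associated with CKD progression, so on the trial's own reasoning the removed placebo patients are among those most likely to lose renal function.

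Two things are at stake. Later eGFR data, and later dialysis or creatinine-doubling events, would be lost from one arm in relation to prognosis. The removed patients would also enter the primary comparison with slopes fitted over a short period, counted the same as slopes over 108 weeks.

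**Working it through.** **1. The plan's own figures.** Inputs: difference 2.7, SD 7.2, one-sided 0.05 and 80% power per stage; two-sided 0.05 overall; 11% withdrawal.
- n per group per stage = 2 × [7.2 × (1.645 + 0.842) / 2.7]² = 87.9. With the t distribution, power is 0.798 at 88 and 0.802 at 89, so 89 is right.
- Overall power with 178 per group is 94.3% by the normal approximation and 94.2% by the t distribution, as stated.
- 89/0.89 = 100 and 178/0.89 = 200 per group, so 400 in total.

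The sample size reproduces and is not affected by this point.

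**2. Which arm the rule reaches.** The highest permitted entry SUA is 10.0, so a patient must rise by at least 12.0 - 10.0 = 2.0 mg/dL. The documents give no exceedance rates, so these are assumptions: baseline SUA normal with mean 7.8 and SD 0.8, truncated to 7.1-10.0; within-patient SD 0.5 to 1.2; 11 post-baseline values; no reduction on placebo and a 20-40% reduction on febuxostat. Simulated chance of any value above 12.0:

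| Within-patient SD | Placebo | Febuxostat, 20% reduction | Febuxostat, 40% reduction |
|---|---|---|---|
| 0.5 | 0% | 0% | 0% |
| 0.8 | 0.07% | 0% | 0% |
| 1.0 | 0.5% | 0% | 0% |
| 1.2 | 2.0% | 0.01% | 0% |

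Of 200 placebo patients, that is 0 to about 4 (0.02 × 200).

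**3. Precision of a truncated slope.** For a per-patient least-squares line, the residual part of the slope variance is σ²/Sxx, where Sxx = Σ(t - mean t)². Times are the Table 2 central creatinine visits (weeks 0, 4, 8, 12, then every 12 weeks to 108), in years.

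| Last visit | Sxx | Variance relative to week 108 |
|---|---|---|
| Week 24 | 0.1246 | 5.777/0.1246 = 46 |
| Week 48 | 0.7019 | 5.777/0.7019 = 8.2 |
| Week 72 | 1.998 | 5.777/1.998 = 2.9 |
| Week 108 | 5.777 | 1 |

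These ratios concern measurement scatter only. The documents do not split the SD of 7.2 into between-patient and residual parts, so the ratios cannot be turned into a new overall SD.

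**4. Effect on the difference if removed patients were wholly lost.** This is an outer case, since their data before removal would in fact be used. Let f be the fraction of placebo lost and g how much steeper their decline is than that of the remaining placebo patients. The remaining difference is 2.7 - f × g. Assumed g is 2.7 (the target effect) to 7.2 (one planning SD). Power is at 178 per group, two-sided 0.05, normal approximation.

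| f | g | Difference | Power |
|---|---|---|---|
| 0.5% | 2.7 | 2.69 | 94.1% |
| 0.5% | 7.2 | 2.66 | 93.7% |
| 2% | 2.7 | 2.65 | 93.4% |
| 2% | 7.2 | 2.56 | 91.8% |
| 5% | 7.2 | 2.34 | 86.6% |

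The 5% row is a stress case above the range in step 2.

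**The case against.** The strongest reply is that a journal article need not describe follow-up after discontinuation, so silence is not a fault. That holds for patients who stop for other reasons. It does not cover the SUA rule, where the article states that participation ends. It can be argued that the sentence loosely means stopping study drug. If so, the repair is one clarified sentence, but as printed it conflicts with the intention-to-treat statement.

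A second reply is that removed patients are not excluded from the analysis. This stands. Urate and creatinine are both scheduled centrally at each visit, so a value above 12.0 mg/dL should come with a post-drug eGFR. The patient then qualifies for the efficacy set, and the slope up to removal is counted. If decline is linear, a truncated slope is noisier but not biased; bias needs the course after removal to differ from the course before it. The figures in step 4 are therefore outer bounds. The direction also matters: losing fast decliners from placebo shrinks the difference, which is conservative for a superiority claim.

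A reader might infer three stronger things that the documents do not support:
- That every patient who stops drug leaves the study. Removal is stated only for SUA above 12.0 mg/dL.
- That the last assessment is analysed as the week-108 value. Footnote a sits on the row labels, most naturally means that final-visit tests are also done at early termination, and says nothing about analysis time.
- That the whole primary estimate is an on-treatment slope. Truncation at stopping is shown only for patients removed by the SUA rule.

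**Conclusion.** The point holds in narrow form. The Blinding section ends study participation on a post-randomisation value that febuxostat lowers, and this is at odds with the intention-to-treat basis of the efficacy analysis. That removals fall almost only on placebo is an inference from mechanism and entry range, supported by a simulation on assumed SUA distributions; the documents give no rates.

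The size is small: 0 to about 4 of 200 placebo patients, and at worst within the 0.5-2% range a difference of 2.56-2.69 with power of 91.8-94.1%, against 2.7 and 94.3% by the same approximation. Any bias from losing the fastest decliners is towards no effect. The incidence of dialysis or creatinine doubling could be more sensitive if events are few, because an event after removal would not be seen; no event rate is given, so this is not quantified. The matter is worth correcting because it is avoidable, not because it threatens the primary result.

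**What to change.** Leave the SUA criterion and the clinical management that follows from it as they are. Reconcile the Blinding and Statistical methods sections as follows:

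1. Patients discontinued under the SUA rule keep the remaining scheduled central creatinine measurements to week 108 unless they withdraw consent.
2. These values enter the per-patient regression in the primary analysis at their actual dates.
3. The Concomitant therapy section states how the prohibition on urate-lowering drugs applies to these patients after they are discontinued.
4. Footnote a of Table 2 states that an early-termination sample is analysed at the time it was taken.

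Cost: there are 11 post-baseline visits, so a patient removed at the first of them has 10 left. With 0 to 4 such patients, that is at most about 4 × 10 = 40 further creatinine samples, taken at visits off study drug. The larger cost is administrative: recruitment closed in December 2013, so this is an amendment to an ongoing trial at 64 institutions.
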